#### Day 30 visit (Day 28–49 post surgery)

The 2nd questionnaire and the 2nd fecal sample collection kit will be mailed to the study participants by the coordinating center 4 weeks after the surgery (Day 28). The study participants are being asked to send back the filled questionnaire and the stool sample to the coordinating center by mail in a prepaid return envelope.

#### Day 90 visit (Day 87–108 post surgery)

The 3rd questionnaire and fecal sample collection kit will be mailed to the study participants by the coordinating center on Day 87 post-surgery, which is the last possible day trial drugs could be used (84 days of treatment + start up to 3 days after surgery). The study participants are being asked to send back the filled questionnaire and the stool sample to the coordinating center by mail in a prepaid return envelope. In addition, the study participants will be asked to send the patient diary to the coordinating center with a prepaid return envelope. Furthermore, they will be asked to donate the 2nd blood sample (38.6 ml). Depending on the distance between the patient’s home and the clinic that recruited them, they will be asked to donate this blood sample either in the clinic or to their general practitioner. In the latter case, all necessary materials will be sent from the coordinating center to them by mail.

#### Month 6 (Day 183–218), year 1 (Day 365–400), and year 2 (Day 730–765) follow-up visits

At these times, staff of the coordinating center will send the study participants the 4th, 5th, and 6th questionnaires. Furthermore, the 4th and 5th fecal sample collection will take place at the month 6 and year 1 visit in the same way as in the visits before.

Furthermore, the coordinating center will contact study participants’ general practitioners and/or oncologists in order to obtain medical records about cancer treatments and infections after release from the hospital and the course of the treatment (incl. re-hospitalizations and cancer recurrence). At the same time, if the staff of the coordinating center was unable to contact a study participant by telephone or mail, the authorities (residents’ registration office, registry office, and/or health authority) will be contacted to find out about the current address and vital status (cause of death, if applicable). If establishing a phone contact with a study participant is difficult, filling out the questionnaires can take place up to 6 months after the planned date.

As the availability of information at authorities about the vital status and cause of death can be delayed by up to 2 years, and the recruitment time will be 2–3 years, we will store the personal data needed for these inquiries for a minimum of 6 years. The obtained overall, cancer, and CRC-specific survival time will vary from 2 to 5 years for the study participants because the mortality follow-up will end at a fixed date (31 Dec 2030). This implies that the last recruited study participant will have the shortest observation period of approx. 2 years, and the first recruited study participant will have the longest observation period of approx. 5 years.

### Data management

#### Electronic case reporting file

For extensive clinical data collection, an eCRF using the ClinicalSurveys.net online platform of the University Hospital of Cologne will be used. ClinicalSurveys.net is hosted by QuestBack, Oslo, Norway, on servers in Cologne, Germany, as part of a software-as-a-service agreement. The proprietary software allows rapid design and deployment of electronic CRFs. Study personnel log in to the system with a username and a safe password including letters, numbers, and symbols. Study personnel can only view and modify their own contributions. All data transmissions are encrypted via TLS 1.2 with an AES 256 GCM bit key and ECDHE RSA key exchange; certificate provided by COMODO RSA Domain Validation Server. Data for the LEONORA study is only documented pseudonymously; no directly identifying data are stored on QuestBack servers.

Administration of the eCRF is limited to selected and named administrators at the University Hospital of Cologne and the coordinating center at the DKFZ, who receive comprehensive training in the system before access is granted. Secure passwords are also enforced for administrators, and they have to regularly change their passwords. Any data manipulation by users and administrators is logged in an audit trail allowing complete data reconstruction. Server administration is performed by QuestBack, and includes regular updates of the linux-based servers, rigid firewall configuration, current virus and threat detection, and daily backups (on-site and off-site with secure storage). Regular on-site audits of security and data protection measures are performed at QuestBack Cologne by the University Hospital of Cologne.

Each study personnel will have specific access and rights defined by their respective role. The system will fulfil standards of Good Epidemiological Practice with state-of-the-art security and data protection standards. Data will be entered accurately and comprehensively by the responsible site personnel. Central and partly automatic monitoring will be performed for plausibility and completeness of data and queries may be issued to the site in case of ambiguity or fault. Data documentation should be performed continuously and at the latest shortly (1 month) after completion of each visit. Data with regard to long-term outcomes will be documented at the respective timepoint.

On-site monitoring of documentation will not be generally conducted at all study sites. However, in case of considerable doubt regarding compliance to study protocol adherence, documentation quality or accuracy, the study coordinators may perform on-site source data monitoring using qualified personnel. During such audits, entries in the eCRF will be compared with the original source documents. The site leader will cooperate in resolving any queries or findings made during the whole monitoring process. A data monitoring committee will not be initiated because the data management team in the University Clinic Cologne, in charge of the monitoring, has enough experienced from previous studies.

The eCRF will be used to collect the following data:

General Information: Study-ID, Age, Sex, weight, height, Inclusion/Exclusion Criteria.CRC information (stage prior surgery, location (ICD-10 code)).Information on patient status (comorbidities, concomitant medication, oncological treatment regimen (chemotherapy incl. number of cycles/ radiotherapy), current location (inpatient, department, ward), known allergies against anti-infective substances, admission, readmission).Information on surgical procedure.Information on clinical events.Detection of MDRO during any local microbiological sampling.Occurrence of consecutive surgeries, including possible repositioning of stoma.Data collected at the study visits conducted while study participants are hospitalized with exception of the questionnaire data.Concomitant medication.Anti-infective treatments.

#### Questionnaire data

Patients will undergo a structured assessment of their quality of life at 6 different time points throughout the study period. Assessment will be performed using the standardized GIQLI, EQ-5D-5 L, EORTC QLQ-C30 core questionnaire and EORTC QLQ-CR29 module [26–29].

The pre-surgery visit questionnaire additionally contains questions about socio-demographic factors and frailty (FRAIL scale [30]). To keep this first questionnaire short, questions on school education, social network (Duke-UNC FSSQ-5 ([31]), co-morbidity, time since the CRC diagnosis, smoking history, and family history of CRC were added to the day 30 questionnaire.

In the day 90, month 6 and month 12 questionnaires, lifestyle questionnaires were added (smoking, alcohol consumption, physical activity, nutrition as well as height and weight for body mass index calculation) using standardized instruments (HEALTHY life-style score [32], Rapid Assessment of Physical Activity questionnaire (RAPA) [33], and the FiberScreen 18-item food frequency questionnaire to assess the amount of fiber in the diet [34]).

Furthermore, questions related to cancer treatments (chemotherapy, radiotherapy, additional surgery), hospitalizations (dates, length and reason), infections (number, location, vaccinations), antibiotics use, and newly developed cancers or CRC reoccurrence (location, date) were added to all follow-up questionnaires from day 90 on.

The questionnaires will be scanned, the scanned information will be verified by visual inspection, and the data will be electronically stored in pseudonymized manner on secured servers in the coordinating center. Scanned information from the pre-surgery visit, day 30, and day 90 questionnaire, needed for the primary and secondary endpoint(s) during the interventional phase of the study, will be verified by two independent documentarists and disagreements will be resolved by inspection of the original questionnaire.

#### Patient diary

The study participants are being asked to document intake of the trial drugs as well as all symptoms, new diagnosed diseases and injuries, which occurred during the 84 days of trial drug intake, in the diary. If compliance with drug intake is unclear, the study participants will be called by phone. If compliance remains unclear (e.g., if study participant cannot be reached), incompliance will be assumed. If the study participants consent to receive SMS massages from the coordinating center and provide their mobile number, they will receive one SMS per week as a short reminder to take the trial drugs and complete the patient diary information for this week.

No trial drug discontinuing criteria, e.g., based on potential adverse events, are stated in the study protocol. As treatment intake is voluntary, the study participants can discontinue treatment at any time, and should document this in the patient diary.

### Biological material

#### Sample collection

Table 3 shows the collected biological specimen at the specific study visits.

**Table 3 Tab3:** Sample collection

Study Visit	Blood samples	Stool suspension samples
Pre-surgery visit	• 1 × 9 ml EDTA tube • 2 × 9 ml Serum tube	• 1 ml COPAN eNAT™ ^a^ • 1 ml COPAN eSwab™ ^a^
Day 30 visit	**-**	• 1 ml COPAN eNAT™ • 1 ml COPAN eSwab™
Day 90 visit	• 1 × 9 ml EDTA tube • 1 × 2.6 ml EDTA tube • 3 × 9 ml serum tube	• 1 ml COPAN eNAT™ • 1 ml COPAN eSwab™
Month 6 follow-up visit	**-**	• 1 ml COPAN eNAT™
Month 12 follow-up visit	**-**	• 1 ml COPAN eNAT™

^a^If no stool sample collection was possible at the pre-surgery visit, rectal swabs will be collected with the same devices

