### Study endpoints

The primary endpoint of the study is the gastrointestinal function-related quality of life 90 days after surgery, as assessed by the Gastrointestinal Quality of Life Index (GIQLI) total score [26].

Secondary endpoints ascertained during interventional study phase.

GIQLI total score 30 days after surgery.GIQLI subscales 30 and 90 days after surgery: symptoms (e.g. diarrhea, flatulence and constipation), physical functions, emotions and social function subscale.Changes in GIQLI total score and sub-scales from pre-surgical visit to day 30 and 90.Low Anterior Resection Syndrome (LARS) Score at day 90 after surgery.Further quality of life total and sub-scales (EQ-5D-5 L, EORTC QLQ-C30, and EORTC QLQ-CR29) 30 and 90 days after surgery and their changes from pre-surgical visit to day 30 and 90.Fatigue scale (EORTC-FA12) and sub-scales at day 90 after surgery.Anxiety (GAD-7) at day 90 after surgery.Cost-effectiveness (costs per prevented diarrhea case) and cost-utility of the intervention (costs per quality adjusted life-year (QALY) gained, as assessed with the EQ-5D-5 L).Emergence of multidrug-resistant organisms (MDRO) until day 90.Rate of physician-documented infections (bloodstream infection (BSI), catheter-related BSI, pneumonia, surgical site infections, intra-abdominal infections, and urinary-tract infections) until day 30 and day 90.Rate of self-reported infections (upper and lower respiratory tract infections, gastro-intestinal tract infections, bladder infections, wound infections, other infections and episodes with high fever (≥ 38 °C)) until day 30 and day 90.Total rate of infection until day 30 and day 90.Antibiotics use (Yes/No and number of days) until day 30 and day 90.Rates of post-operative complications, defined as the following 4 clinical events: Initiation of antibiotic or antifungal treatment, surgical revision, new mechanical ventilation, sepsis or death until day 90.Time from CRC surgery to hospital discharge.Number and length of re-hospitalizations until day 90.Changes in the gut microbiome composition until day 30 and day 90.Concentration changes of biomarkers of inflammation and immune function in serum samples collected prior surgery and 90 days after surgery (89 proteins of the combination of the OLINK^®^ Target 48 Cytokine panel and the OLINK^®^ Target 48 Immune Surveillance panel, including, for example, interleukin-6 as well as biomarkers of systemic inflammatory response (C-reactive protein (CRP), mGPS (modified Glasgow prognostic score), HS_mGPS (high-sensitive mGPS), NLR (neutrophil-to-lymphocyte ratio), PLR (platelet-to-lymphocyte ratio), LMR (lymphocyte-to-monocyte ratio), SII (systemic immune-inflammation index), PNI (prognostic nutritional index), and NPS (neutrophil-platelet score))).Concentration changes of metabolomic biomarkers (pre-defined selection of amino acids, fatty acids, and bile acids measured with high accuracy with targeted LC-MS/MS and the total metabolome measured with untargeted LC-MS/MS, which has lower accuracy) in fecal and plasma samples collected prior surgery and 90 days after surgery.

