#### Pre-surgery visit for information about the study (Day − 13 prior surgery to day of surgery)

During a first appointment in the hospital, eligible patients will be informed about the LEONORA study and the secondary data use in the National Center for Tumor Diseases (NCT) network by a study physician and will receive the printed study information documents. Written informed consent to participate in the LEONORA study will be obtained.

A study nurse or study physician will pick the baseline questionnaire from a study package, which is labelled with the RandomID, and give it to the study participant who shall fill it on the same day while being in the clinic. It is important that the study nurse takes a package with a RandomID starting with the letter “K” for a colon cancer patient or with a RandomID starting with the letter “R” for a rectum cancer patient. If a patient has both colon and rectum cancer, a package with a RandomID starting with a “K” shall be picked.

The study nurse or study physician will collect the baseline questionnaire, check it for completeness and will ask the study participant to complete the missing items immediately. The questionnaire will collect important data on the baseline levels of the quality of life endpoint scales and information needed to be able to contact the study participants for the follow-ups (name, sex, birthday, address and phone number).

Furthermore, the first stool sample will be collected on the Day − 13 to Day − 1 prior, with swabs that are labelled with the RandomID. If study participants cannot donate a stool sample in the given time frame, they will be asked to collect a rectal swab. The fecal sample should be obtained prior to the initiation of laxative treatment if performed pre-operative as part of routine patient management standards. Furthermore, 27 ml blood will be taken from each patient on the same day using tubes labelled with the RandomID. If possible, the blood sampling will be included in a regular blood sampling that is needed anyway for the routine patient care.

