#### Sample Storage

All study sites will collect, process, and store samples in local freezer storage at temperatures between − 32 °C to -80 °C in boxes or crates. The samples will be sent to the laboratory of the coordinating center in batches every 6 months. All samples can be stored for up to 30 years and must then be destroyed or disposed.

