Incompliance: Defined as intake of trial drugs on less than 80% of the treatment days (i.e., < 67 days) as documented in the patient diary. If no patient diary was sent back to the coordinating center, this also counts as incompliance.Late completion of the day 90 questionnaire: Defined as > 115 days after surgery.Use of probiotic product in addition to the study medication (i.e., any time between post-surgery and day 90 visit).Late noticed false inclusion in the trial (inclusion criteria not fulfilled or exclusion criterion was present).

All secondary endpoints with a continuous scale will be analyzed with the same statistical methods as described for the primary endpoint above, with a linear regression model adjusting for center and the baseline value of the endpoint (if accessed). The dichotomous secondary endpoints will be tested with a logistic regression model or Cox proportional hazards regression model (depending on the nature of the endpoint) adjusted for center. In addition, a generalized estimating equation (GEE) model will be applied for all outcomes that have been repeatedly assessed.

The following a priori defined subgroup analyses will be conducted (The definition of pre-operative is “Assessed at pre-surgery visit,” and the definition of peri-operative is “Ascertained between pre-surgery visit and day 90 visit”):

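### Fecal changes from baseline mix biology with specimen type and handling, and the single baseline covariate costs some precision (minor, exploratory endpoints only)

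*Protocol article*

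**What the plan says.** The section Study endpoints of the protocol article lists two fecal outcomes as changes: "Changes in the gut microbiome composition until day 30 and day 90", and "Concentration changes of metabolomic biomarkers", the latter measured "in fecal and plasma samples collected prior surgery and 90 days after surgery". Microbiome change is also followed to months 6 and 12.

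The pre-surgery sample is not always stool. The section on the pre-surgery visit says: "If study participants cannot donate a stool sample in the given time frame, they will be asked to collect a rectal swab". The footnote to Table 3 (Sample collection) repeats this: "If no stool sample collection was possible at the pre-surgery visit, rectal swabs will be collected with the same devices". The footnote is attached to the pre-surgery row only.

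Handling also differs by visit. Under Sample Storage, "All study sites will collect, process, and store samples in local freezer storage", with shipment in batches every 6 months. At day 90 the participant returns "the stool sample to the coordinating center by mail in a prepaid return envelope". The day 30 section describes the same route, and months 6 and 12 follow the earlier visits.

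The section Statistical analysis plan analyses continuous secondary endpoints "with a linear regression model adjusting for center and the baseline value of the endpoint", where a baseline was assessed. It also plans 95% confidence intervals for all outcomes in each group, and it regards everything except the primary endpoint as exploratory.

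**The concern.** A change from baseline is easy to read only if both ends are measured in the same way. Here they differ in two respects. For some patients the first specimen is a rectal swab and the later ones are stool. For apparently every patient the first specimen is frozen at the site and the later ones travel by post.

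Two consequences follow. First, a within-arm change cannot be read as loss or recovery of the microbiome or metabolome, because part of it may come from specimen and transport. The Discussion presents faster microbiome recovery as an expected benefit, so readers will be drawn to such a reading. Second, if swab and stool values differ in level, or in how well they predict the day 90 value, a single slope on the pooled baseline is a weaker covariate than it need be. The between-arm estimate is then less precise.

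**Working it through.** **The plan's own figure.** No sample size or precision is stated for the fecal endpoints. The only relevant figure is the analysed number for the primary endpoint. A difference of 77.0 − 72.5 = 4.5 with SD 9.9 gives 77 per arm by the exact t-test (power 0.8003; 76 per arm gives 0.7950). That is 154 analysed, and 154 / 0.75 = 205.3, so 206 randomised. It reproduces and is not affected. I use 77 per arm below.

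**Within-arm change.** Let p be the swab share, d the swab-minus-stool shift at baseline, and h the shift from posting at follow-up, all in SD units. With no true change, the expected observed change in either arm is

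h − p·d.

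The article gives none of these values. Assumed examples:

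| p | d | h | apparent change |
|---|---|---|---|
| 0 | 0 | +0.5 | +0.50 |
| 0.10 | +0.5 | +0.5 | 0.5 − 0.05 = +0.45 |
| 0.30 | +1.0 | +0.5 | 0.5 − 0.30 = +0.20 |
| 0.50 | +1.0 | +0.5 | 0.5 − 0.50 = 0.00 |
| 0.10 to 0.40 | −1.0 | 0 | +0.10 to +0.40 |

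The two artefacts can add or cancel, so the direction of an observed change is no guide either.

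**Between-arm contrast.** The term h − p·d has the same expectation in both arms: baseline precedes treatment, allocation is randomised and blinded, and both arms use the same return route. In a simulation of 4,000 trials per scenario with 77 per arm, the stated model (without the center terms) gave a mean estimate of about 0.00 under no effect and about 0.40 under a true effect of 0.4 SD. Type I error was 4.5-5.6%.

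**Precision.** Assume within-type variance 1, baseline-to-follow-up correlation 0.6 for stool and 0.3 for swab, and a swab shift of size d. The residual variances are

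- one pooled baseline: 1 − [0.6(1−p) + 0.3p]² / [1 + p(1−p)d²]
- specimen type plus interaction: 1 − [0.36(1−p) + 0.09p]

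For p = 0.20 and d = 1, the pooled value is 1 − 0.54²/1.16 = 0.7486 and the specimen-specific value is 1 − 0.306 = 0.694. The ratio is 1.079. Ratios over the range:

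| p | d = 0 | d = 1 | d = 2 |
|---|---|---|---|
| 0.05 | 1.007 | 1.030 | 1.090 |
| 0.10 | 1.012 | 1.052 | 1.141 |
| 0.20 | 1.021 | 1.079 | 1.185 |
| 0.30 | 1.026 | 1.089 | 1.191 |
| 0.40 | 1.029 | 1.089 | 1.180 |

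These ignore the cost of estimating two extra terms. A simulation with 77 per arm and 6,000 trials per cell includes that cost. It gave 1.00-1.02 with no shift, 1.02-1.09 with a 1 SD shift and 1.08-1.19 with a 2 SD shift. A 2-19% excess in variance widens the confidence interval by about 1-9% (√1.02 = 1.01, √1.19 = 1.09).

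**Other assumptions.** With a common correlation of 0.5, a true effect of 0.4 SD, 30-50% swabs and a 1 SD shift, power was about 0.78 with the pooled baseline and about 0.80 with a specimen-type term.

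**The case against.** The strongest reply is that nothing confirmatory is at risk. The randomised contrast is unbiased, the precision loss is modest, and the endpoints are declared exploratory. That stands, and it is why the point is minor.

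It is also fair that every driving input is assumed. The swab is a fallback, so 40% is an upper case without support in the text. The article gives no figure for a stool-swab difference, uses the same devices for both, collects the pre-surgery stool itself with swabs, and asks for sampling before laxatives. This may shrink the shift. It does not make the two specimens the same, nor does it touch the freezer-post difference.

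The plan states no within-arm test, so a false-positive rate for within-arm change would describe a test that nobody proposes. Only the planned intervals in each arm are affected. Baseline also precedes surgery and its antibiotics, so within-arm change could not isolate the synbiotic in any case.

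Some stronger readings are tempting but unsupported:

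- A reader might infer that the treatment effect on fecal endpoints is biased. That would need handling to act differently on the composition produced by treatment, and the documents give no basis for sizing it.
- A reader might infer that one tube must stay viable for culture and so lets metabolites drift. Table 3 lists two devices at baseline, day 30 and day 90, and the article does not say which serves culture or metabolomics.
- A reader might infer that the single-slope problem covers all microbiome results. The linear model is stated for continuous endpoints; no test for multivariate composition is given.

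Finally, the abbreviations list a sample manual, and a separate analysis plan may exist. Recording fields may stand there, so their absence from the article is no fault. What remains is how the stated elements combine: change endpoints, a mixed baseline, a different follow-up route and one undifferentiated baseline covariate.

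**Conclusion.** The point holds as a minor one, for exploratory endpoints only. Within-arm change in fecal metabolites and in continuous microbiome measures, with its 95% interval, cannot be separated from specimen type and handling. The between-arm contrast is not biased by a shift common to both arms, but the stated model gives up some precision: roughly 2-19% extra variance with 5-40% swabs, a 1-2 SD shift and correlations of 0.6 and 0.3, and at most about 3% if there is no shift. These sizes rest wholly on assumed values. That baseline samples are frozen at the site is read from the storage section together with the visit sections; the article does not say where the baseline stool is passed.

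**What to change.** In the models for continuous fecal endpoints, add baseline specimen type (stool or rectal swab) and, where the number of swabs allows, its interaction with the baseline value. State that conclusions rest only on the between-arm difference, at day 30 and day 90 for the microbiome and at day 90 for metabolites. Report within-arm change as descriptive only. Add a sensitivity analysis restricted to patients with a stool baseline, noting that the freezer-post difference remains in it.

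The cost is one or two more model terms and less emphasis on within-arm change. With few swabs and no shift the extra terms gain almost nothing, so the interaction can be dropped when swabs are rare. No extra sample or procedure is needed. Whether a baseline was stool or swab has to be known for each patient; if the sample manual does not already record it, one field is added.
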